#### TAU

Though treatments for depressive and anxiety disorders in Japanese medical settings have not been systematically investigated, the majority seem to involve pharmacotherapy, unsystematic supportive therapy, or clinical monitoring by psychiatrists. The Japanese Society of Mood Disorders has published treatment guidelines for Major Depressive Disorders (MDDs) that recommend pharmacotherapy for moderate or severe MDD patients and pharmacotherapy and psychotherapy for mild MDD patients [70]. However, there are no such treatment guidelines for anxiety disorders specific to Japanese clinicians. One study showed that Japanese psychiatrists tend to choose pharmacotherapy for the first and second instance of treatment of MDD [71], and the results of our pilot study showed that almost all participants had received pharmacotherapy [68]. Based on the knowledge, we expected TAU for depressive and anxiety symptoms to be mostly pharmacotherapy. For this clinical trial, we defined TAU as any pharmacological or (non-systematic) psychological intervention except for systematic psychotherapy (e.g., any other type of cognitive behavioral therapy) and electroconvulsive therapy. We considered that the clinical success of participant’s treatment should be prioritized over our research purpose. Hence, we will not restrict any usual treatment by treating psychiatrists, including change of dose or type of drug. If treating psychiatrists start other systematic psychotherapy (e.g., another type of cognitive behavioral therapy) or electroconvulsive therapy, the patient will be excluded from the intervention in this study. Content of TAU will be documented in case report form.

### Follow-up phase

We set the assessment period at 43 weeks in order to exploratorily examine the trajectory after treatment for the intervention group. Participants assigned to the control group will receive the unified protocol in addition to TAU during the follow-up period (21–43 weeks). Data including the 43-week assessment will be used to exploratorily examine the persistence of the effect for the intervention group as well as the immediate treatment effect for the control group. There will be no treatment restrictions on the intervention group in the follow-up period.

### Discontinuation

Any participant in the intervention group who meets any of the discontinuation criteria will have their intervention (UP) stopped. Where possible, subsequent assessment will be conducted.Participant request for discontinuation or participant withdrawal of consent.Inability to contact the participant for a month.Difficulty continuing the intervention because of a severe adverse event.Difficulty continuing the intervention because of the exacerbation of comorbid symptoms.Participant proves after assignment not to fulfill the eligibility criteria.The whole clinical trial is stopped.Any other reason that the primary investigator, therapist, and supervisor agree to warrants discontinuation.

### Measures

We will assess several measures of outcome, treatment mechanism, process, and neurological correlates. Most assessments will be conducted at baseline (0 weeks), 10 weeks (mid assessment), 21 weeks (post assessment), and 43 weeks (follow-up assessment). Table 2 shows the list and schedule of assessments.

#### Primary outcome

The primary outcome is change of depressive symptoms over the intervention period as assessed by the 17-item version of the semi-structured interview included in the GRID–Hamilton Depression Rating Scale (GRID-HAMD) [72–74]. GRID-HAMD employs a “grid” scoring system using the dimensions of symptom intensity and symptom frequency; higher scores indicate severer depressive symptoms (range: 0–52). This interview instrument has been reported to have excellent interrater reliability among Japanese clinicians (intraclass correlation coefficient; ICC = 0.95–0.99) [73], a finding borne out by our pilot study (ICC = .974, 95%CI = .966–.980) [68]. Internal consistency was reported to be 0.78 [74]. The interview instrument’s concurrent validity was demonstrated by high correlation between item and total score per the structured interview guide for HAMD [74]. We decided to use GRID-HAMD to assess “emotional symptoms” because it assesses not only depressive symptoms (depressed mood, guilt, suicide, insomnia early, insomnia middle, insomnia late, work and activities, psychomotor retardation, psychomotor agitation, loss of appetite, loss of sexual interest, loss of weight, and loss of insight) but also anxiety symptoms (psychic and somatic anxiety, general somatic symptoms, and hypochondriasis). Moreover, the GRID-HAMD is an appropriate choice for our study because it is one of the few depression rating measures that has been validated in Japanese and utilized in many clinical trials in Japan [75, 76], making implementation of assessment more straightforward. In our pilot study, we used GRID-HAMD and the Structured Interviews Guide for Hamilton Rating Scale for Anxiety (SIGH-A) as outcome measures. The result showed the GRID-HAMD showed higher treatment responsiveness than SIGH-A [68].

#### Secondary outcomes

Secondary outcomes for treatment efficacy are severity of anxiety assessed by SIGH-A, overall severity and improvement rated by Clinical Global Impression, responder status defined by 50 % or more baseline reduction in score on GRID-HAMD, remission of symptom defined as less than 8 on GRID-HAMD [77], and absence of met psychiatric diagnoses as assessed by SCID-IV-TR at baseline. These secondary measures are assessed at post-treatment (21 weeks).

#### SIGH-A

A semi-structured interview, SIGH-A includes 14 items for anxiety symptoms [78, 79]. Each anxiety-related item is rated from 0 to 4 on the basis of frequency, degree of distress, and symptom-related functional impairment during the previous week. Higher scores indicate more severe symptoms of anxiety (range: 0–56). Test–retest reliability and interrater reliability were respectively reported as 0.89 (95 % CI 0.83–0.93) and 0.99 (95 % CI 0.98–0.99). Concurrent and construct validity were demonstrated by high correlation with the traditional-format Hamilton Anxiety Rating Scale (*r* = 0.75–0.77) and equivalent correlations with self-report measures in the traditional format [78].

#### Clinical Global Impression (CGI)

CGI is an overall clinician rating of the severity of psychopathology (CGI-Severity; CGI-S) and improvement of it (CGI-Improvement, CGI-I) [80]. These are rated from 0 to 7 based on the assessor’s overall evaluation, which incorporates all available information about a patient’s history, psychosocial circumstances, symptoms, behavior, and the impact of symptoms on the patient’s ability to function [81]. In this study, essentially, the independent evaluator assesses the same patient at baseline, mid, post, and follow-up (0, 10, 21, and 43 weeks). Hence, the evaluator’s overall impression of longitudinal change will be reflected in the CGI-I rating.

#### Global Assessment of Functioning (GAF)

The GAF is a single measure for evaluating degree of global functioning, which is used for Axis V evaluation in DSM-IV [82]. A score is assigned from 0–100, based on symptom severity and the effects on social, occupational, and/or educational functioning.

#### Structural clinical interview for DSM-IV-TR axis I disorders (SCID-IV-TR)

SCID-IV-TR is a semi-structured interview used to asses the diagnostic status of DSM-IV-TR Axis I disorders [83]. We will administer modules A (Mood Episodes), B (Psychotic Symptoms), D (Mood Disorders), E (Substance Use Disorders), and F (Anxiety Disorders) at baseline to evaluate patients according to the inclusion and exclusion criteria. At post-intervention and follow-up, the independent evaluator administers part of each module to examine the presence or absence of the diagnoses met at baseline assessment. The Japanese version of *SCID-IV-TR* has been utilized in many clinical trials since its publication.

#### Overall Anxiety Severity and Impairment Scale (OASIS)

OASIS assesses the symptom of global anxiety by severity and impairment, using a (five-point) Likert scale [84, 85]. Items cover anxiety frequency, severity, and influence on symptoms. OASIS’s reliability and validity have been reported among U.S. and Japanese clinical and non-clinical populations [68, 84].

#### Overall Depression Severity and Impairment Scale (ODSIS)

ODSIS assesses the symptom of depression in terms of severity and impairment [86], on a (five-point) Likert scale. Similarly to OASIS, this scale assesses depression frequency, severity, and related impairment. Two studies suggest its reliability and validity among U.S. and Japanese clinical and non-clinical populations, respectively [86, 87].

#### Disorder-specific measures

In accordance with the diagnosis by SCID-IV-TR at baseline, each patient conducted the self-report measures to assess symptoms of met diagnoses. We used the Beck Depression Inventory-II (BDI-II) for Depressive Disorders [88, 89], Panic Disorder Severity Scale (PDSS) for Panic Disorder with or without Agoraphobia [90], Liebowitz Social Anxiety Scale (LSAS) for Social Anxiety Disorder [91], Penn State Worry Questionnaire (PSWQ) for Generalized Anxiety Disorder [92], Yale–Brown Obsessive Compulsive Scale (Y-BOCS) for Obsessive Compulsive Disorder [93], Impact of Event Scale-Revised (IES-R) for Posttraumatic Stress Disorder [94, 95], and Fear Questionnaire (FQ) for Agoraphobia without history of Panic Disorder [96]. All scales except for FQ have had their reliability and validity tested.

#### Euro Qol (EQ-5D-3L)

Patient quality of life is assessed by Euro Qol (EQ-5D-3L) [97, 98]. This scale consists of five items in the domain of quality of life (mobility, self-care, usual activities, pain/discomfort, and anxiety/depression) and one visual analogue scale regarding overall health status, ranging from 0 (worst imaginable health state) to 100 (best imaginable health state). Quality-adjusted life years will be calculated using the Japanese EQ-5D tariff [98].

#### Sheehan Disability Scale (SDS)

SDS is used to assess overall functional impairment [99, 100]. This scale consists of three domains of function (work/school, social life, and family life/home responsibilities). These items are rated on a 10-point visual analogue scale (from “not at all” to “extremely”). Its reliability and validity for a Japanese population has been reported [100].

#### Sense of Authenticity Scale (SOA)

SOA assess one’s sense that one is being true to oneself. It comprises seven items to be answered on a (five-point) Likert scale (1: Strongly disagree–5: Strongly agree). This scale was originally developed among a Japanese population [101]. Research in personality, social psychology, and positive psychology has suggested that authenticity can be conceptualized as a healthy type of self-esteem [101, 102] and can serve as an indicator of positive functioning [103]. Its reliability and validity has been repeatedly reported among Japanese population [101, 104].

#### Treatment mechanism

##### Neuroticism subscale of the Eysenck Personality Questionnaire Revised–Short-Form (EPQR-S)

Neuroticism is the tendency to experience negative affect frequently and intensely, which is a putative transdiagnostic factor for persistence of emotional disorders. This scale assesses this personality tendency using 12 dichotomous items. Its reliability and validity has been shown in the U.S. and in Japanese [105, 106].

##### Anxiety Sensitivity Index-3 (ASI-3)

ASI-3 is a self-report questionnaire for assessing beliefs about the feared consequences of symptoms associated with harmful physical, cognitive, or social concerns [107]. The questionnaire consists of 18 items evaluated on a four-point Likert-type scale (0: very little; 4: very much). The measure possesses excellent psychometric properties, performing well on various indices of reliability and validity [107].

##### Emotion Regulation Skills Questionnaire (ERSQ)

ERSQ assesses how the respondent has dealt with negative emotions in the previous week [108]. This 27-item questionnaire has nine subscales: awareness, clarity, sensation, understanding, compassionate self-support, modification, acceptance, tolerance, and readiness to confront. Each subscale comprises three items, measured on a (five-point) Likert scale (0: not at all; 4: almost always). The scale demonstrates sufficient reliability and validity [108].

##### Emotion Exposure Questionnaire (EEQ)

EEQ was originally developed to assess overall patient tendency to expose themselves to their own emotions, which is understood to be a hallmark of the treatment mechanism of the unified protocol. The items represent willingness or ability to expose oneself to emotions (e.g., “Even if it is distressing, I try to feel the emotion fully”). This questionnaire consists of thirty items evaluated on a (five-point) Likert-type scale.

##### Treatment Rationale of Unified Protocol (TRUP)

TRUP was originally developed to assess comprehension of treatment rationale for the unified protocol. It consists of 12 statements to be answered yes or no. We developed two items for each treatment module (psychoeducation of emotion, emotional awareness, cognitive reappraisal, emotion avoidance and emotion-driven behavior, tolerance of physical sensation, and emotion exposure). A sample item regarding psychoeducation of emotion is “It is better to suppress emotion and feelings and try not to feel it.”

#### Process measures

##### Session Rating Scale (SRS)

SRS is used to assess the therapeutic alliance [109]. It consists of four visual-analogue items (bond, consensus of task, consensus of goal, and overall evaluation). These item are consistent with the conceptualization of the “working alliance” and have good psychometric properties in terms of reliability and validity [109].

##### Credibility/Expectancy Questionnaire (CEQ)

CEQ assesses the patient’s perception of the credibility of treatment and expectancy regarding treatment. It measures cognitive and emotional aspects of credibility and expectancy, using six items. Because there was no Japanese version of this questionnaire, we translated it using a rigorous back-translation procedure, with the permission and support of the original developer of this questionnaire.

##### Homework Compliance Scale (HCS)

HCS is a single measure for the therapist to assess the patient’s degree of completion of their homework [110]. Therapists who conduct the unified protocol assess patient homework compliance at the end of every session, using 0–6 anchors. We translated this measure using a back-translation procedure, with permission and support from one of the original authors of the scale.

#### Adverse events, treatment, and assessment integrity

We defined adverse events to include any undesirable physical or psychological event during the research period, irrespective of its relation with the intervention. Using the forms described above, therapists or independent evaluators solicit patients at each visit for assessment of occurrence or worsening of the following symptoms: dry mouth, astriction, dysuria, accommodation disorder, orthostatic hypotension (dizziness, lightheadedness), sleepiness, malaise, insomnia, anxiety/irritation, asitia, weight gain or loss, loss of sexual interest, suicidality, suicidal attempt, and other symptoms. We assessed the severity of the adverse event using criteria from the Japanese version of the Common Terminology Criteria for Adverse Events (CTCAE v4.0) [111]. This rating system uses a (five-point) Likert-type scale (1: Grade 1, Mild; 2: Grade 2, Moderate; 3: Grade 3, Severe or medically significant but not immediately life-threatening; 4: Grade 4, Life-threatening consequences; 5: Grade 5, Death). A “severe” adverse event is defined as one with a 3 or higher severity rating.

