Time points (week)	0	1	2	3–4	5	6–9	10	11–14	15	16–20	21	43
Outcomes (evaluator rating)												
GRID-Hamilton Rating Scale for Depression	IE						IE				IE	IE
Structural Interview Guide for Hamilton Anxiety Rating Scale	IE						IE				IE	IE
Clinical Global Impression	IE						IE				IE	IE
General Assessment of Functioning	IE						IE				IE	IE
Structural clinical interview for DSM	IE										IE	IE
Outcomes (self-report)												
Overall Anxiety Severity and Impairment Scale	P	P	P	P	P	P	P	P	P	P	P	P
Overall Depression Severity and Impairment Scale	P	P	P	P	P	P	P	P	P	P	P	P
Disorder Specific Measures	P						P				P	P
EQ-5D	P						P				P	P
Sheehan Disability Scale	P						P				P	P
Sense of Authenticity Scale	P						P				P	P
Treatment mechanism												
Eysenck Personality Questionnaire Revised-Short version, Neuroticism subscale	P				P		P		P		P	P
Anxiety Sensitivity Inventory-III	P				P		P		P		P	P
Emotion Regulation Skills Questionnaire	P				P		P		P		P	P
Emotion Exposure Questionnaire	P				P		P		P		P	P
Treatment Rationale for Unified Protocol	P				P		P		P		P	P
Process measures												
Session Rating Scale		P/T			P/T		P/T		P/T			
Credibility/Expectancy Questionnaire			P/T									
Homework Compliance Scale			T	T	T	T	T	T	T	T		
Adverse Event			T	T	T	T	T/IE	T	T	T	IE	IE
Neurological correlates												
Functional Magnetic Resonance Imaging	X										X	X

*IE* assessment of independent evaluator, *P* patient self-report, *T* therapist self-report

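### Adverse events are recorded as new or worse symptoms, but the checklist is not scheduled at week 0, so for six drug-type symptoms the first judgement rests on recall, over intervals that appear to differ by arm

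*Protocol article*

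**What the plan says.** The section on adverse events defines an event as "any undesirable physical or psychological event during the research period, irrespective of its relation with the intervention". It then describes a solicited checklist: "therapists or independent evaluators solicit patients at each visit for assessment of occurrence or worsening of the following symptoms". Fourteen symptoms are named, plus an open category, and severity is graded on CTCAE v4.0.

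Table 2 gives the timing. The header is "Time points (week) 0 1 2 3–4 5 6–9 10 11–14 15 16–20 21 43" and the row is "Adverse Event T T T T T/IE T T T IE IE". Once the blank cells are aligned, weeks 0 and 1 are empty. Therapist entries run from week 2 to weeks 16–20, and the evaluator has entries at weeks 10, 21 and 43.

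The TAU section reports that "the results of our pilot study showed that almost all participants had received pharmacotherapy" and that "we will not restrict any usual treatment by treating psychiatrists, including change of dose or type of drug". The Follow-up phase section gives controls UP only between weeks 21 and 43.

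**The concern.** A symptom can be called new or worse only against an earlier state. Table 2 schedules no recording of that state on the checklist or on the CTCAE grade. The gap matters in this population. Most patients are expected to be on medication when they enter, and several checklist symptoms are complaints that a medicated patient may already have. Entry also requires a GRID-HAMD score of at least 8, so some of the illness symptoms on the list will be present at the start.

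What is at stake is how the safety data can be read. Without a recorded starting grade, the first report of a drug-type symptom mixes what is new with what the patient remembers as new. If the two arms are first asked at different times, the quality of that memory may differ between them.

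**Working it through.** No power or sample size figure enters this point. The check sets the schedule, the checklist and the baseline measures side by side.

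**1. Are the blank cells real?** The Table 2 header and the adverse event row each have 13 fields (a label and 12 time points), so the row has not shifted. The GRID-HAMD row, read the same way, falls at weeks 0, 10, 21 and 43, which agrees with the Measures section.

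**2. Were there contacts at which the checklist could have been taken?** Yes. The evaluator rates GRID-HAMD at week 0, and the Session Rating Scale row has a patient and therapist entry at week 1. Neither contact has an adverse event entry, so the table does not match a text that calls for enquiry at every visit.

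**3. When is each arm first asked?** Table 2 does not separate the arms. Its legend marks T as the therapist, and controls have no UP therapist before week 21.

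| Arm | First enquiry | Interval from week 0 |
|---|---|---|
| UP with TAU | therapist, week 2 | 2 − 0 = about 2 weeks |
| Waiting-list with TAU | evaluator, week 10 | 10 − 0 = about 10 weeks |

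**4. Which symptoms have another baseline record?** The 14 named symptoms were compared with the GRID-HAMD items listed under Primary outcome.

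| Checklist symptom | Week-0 GRID-HAMD item |
|---|---|
| insomnia | three insomnia items |
| anxiety/irritation | psychic and somatic anxiety |
| asitia | appetite item |
| weight gain or loss | weight item, loss only |
| loss of sexual interest | same |
| suicidality; suicidal attempt | suicide item |
| malaise | general somatic symptoms, approximate |
| sleepiness, dry mouth, dysuria, astriction, orthostatic hypotension, accommodation disorder | none listed |

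Count: 8 with a full or approximate match + 6 with none = 14. If the match for malaise is rejected, the split is 7 and 7. None of the 14 has a scheduled CTCAE grade at week 0.

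**5. How many target patients could still benefit?** The target is 54, and 44 were enrolled when the article was submitted: 54 − 44 = 10 (10/54 = 19%). Any patients recruited beyond the target for the ancillary work would be additional.

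**The case against.** The case on the other side is substantial, and much of it limits the point.

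- **The question itself asks about change.** A reader might infer that existing symptoms will be counted as events, or that new events cannot be told from old complaints. The text does not support either. A rater who follows it would not record an unchanged symptom. The weakness is reliance on recall.
- **Worsening later in treatment can be shown.** A reader might infer that no deterioration during UP could be documented. From week 2 the therapist asks repeatedly and events are graded, so the undocumented stretch in the UP arm is weeks 0 to 2.
- **Illness symptoms have a baseline.** Suicidality in particular is rated at week 0 and used for exclusion. This stands, except that GRID-HAMD scores are not CTCAE grades and weight gain is not covered. SIGH-A is also rated at week 0. Its items are not listed, so further overlap can be neither shown nor excluded.
- **The number affected is unknown.** It is tempting to multiply an assumed prevalence by the 27 patients per group. The documents give no prevalence, and the product would describe existing complaints, not misclassified events.
- **Randomisation balances existing complaints on average.** True, so the missing baseline alone mainly adds noise. Randomisation does not equalise how long each arm must think back, so misclassification may differ by arm. The documents do not show in which direction.
- **Adverse events are not an efficacy outcome, and the article is condensed.** The first part is correct. On the second, a baseline form in the case report forms cannot be excluded. The article does print a schedule for this checklist, however, and that schedule omits week 0. This is more than detail left to a fuller document.

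**Conclusion.** The point holds in limited form. The schedule fixes a change measure without a recorded starting grade. For at least six of the 14 named symptoms, no listed GRID-HAMD item fills the gap, so the judgement at the first enquiry rests on recall. That recall spans about 2 weeks in the UP arm and about 10 in the control arm. The illness symptoms are largely covered at week 0, though not on the grade used for adverse events.

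This rests on three assumptions: that therapist entries before week 21 apply to the UP arm only, that no baseline checklist exists in forms not shown, and that general somatic symptoms is accepted as an approximate match for malaise. The primary efficacy analysis is untouched. The consequence is confined to how safely adverse event counts can be read and compared, and its numerical size cannot be derived from the documents. The correction is cheap enough to be worth making.

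**What to change.** - Add the same checklist, with CTCAE grades, at the existing week-0 evaluator visit, before allocation, for every patient still to be enrolled. Show it in Table 2 and reconcile the wording on enquiry at every visit with the table.
- Use the week-0 record as the reference for occurrence or worsening. Still count a symptom that resolves and then recurs, even at its starting grade. A rule that required the grade to exceed week 0 would miss such events and could under-count harm.
- For patients already enrolled, use the week-0 GRID-HAMD items where they exist. Report the other symptoms found at the first enquiry as present or recall-based, separately from events with a recorded baseline.
- If a baseline form already exists, cite it and state that it is the reference.

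The cost is one form at an existing visit and a few minutes per patient. The limits should be stated: the 44 patients already enrolled get only a partial correction, so the report will carry two kinds of reference and must label them. A week-0 form gives both arms the same starting point but does not make later enquiry equally frequent, which is a separate matter.

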### Intervention

We compare the UP with TAU intervention group with the waiting-list with TAU control group.

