#### UP

UP is an transdiagnostic cognitive behavior therapy for emotional disorders [35]. Complete implementation usually takes 12–18 weekly sessions of 50–60 min each. Patient use the treatment workbook throughout the treatment [69], and practice newly learned cognitive-behavioral skills in between sessions. In this study, patients will receive approximately 16 face-to-face, individual sessions (range: 9–20) within 20 weeks. The therapist can shorten or lengthen needed sessions or intervals (weekly or biweekly) in accordance with the patient’s level of understanding or acquisition of the skills. Up to five additional sessions during the follow-up period for the intervention group will be allowed if the therapist and patient deem it necessary and if the patient has not completed all modules.

The unified protocol consists of one introductory session and eight modules for learning transdiagnostic cognitive behavioral skills: motivation enhancement, psychoeducation of emotion, emotion awareness training, cognitive reappraisal, emotion avoidance and emotion-driven behavior, tolerance training for physical sensations, emotion exposure, and relapse prevention (Table 1). Details of this intervention are described in the therapist’s guide to UP [35]. To be eligible for this clinical trial, a therapist needs to be qualified as a clinical psychologist by the Foundation of the Japanese Certification Board for Clinical Psychologists or possess a Japanese physician’s license, to have received adequate training using the therapist’s guide for UP and the CBT treatment manual published by the Japanese Ministry of Health, Labour and Welfare (at least 10 h of workshops), and to sit in on or listen to the full treatment course of at least two UP cases. At the beginning of this trial, four therapists (two females; clinical practice after certification of 4–6 years; experience of UP cases, 3–8 cases) were registered as staff therapists.

**Table 1 Tab1:** Outline of Unified Protocol

Numbers of sessions needed	Module
1	Introduction to treatment
1–2	Motivation enhancement
1–2	Psychoeducation of emotional experiences
1–2	Emotion awareness training^a^
1–2	Cognitive appraisal and reappraisal^a^
1–2	Emotion avoidance and emotion-driven behaviors^a^
1	Awareness and tolerance training for physical sensations^a^
4–6	Emotion exposure^a^
1	Relapse prevention

^a^ Core modules

**Table 2 Tab2:** Schematic diagram for the schedule of assessments

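### Up to week 21, the UP arm is asked about adverse events at each session from week 2 and by the evaluator, the waiting list only by the evaluator, so pooled counts by arm would tend to run higher under UP

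*Protocol article*

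**What the plan says.** The section on adverse events, treatment and assessment integrity counts any unwanted physical or psychological event in the research period, whether or not UP caused it. It sets the collection rule: "therapists or independent evaluators solicit patients at each visit for assessment of occurrence or worsening of the following symptoms". The list that follows includes insomnia, anxiety, malaise, sleepiness, weight change, loss of sexual interest and suicidality. No other person is given this task, and the article states no look-back period.

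The schedule in Table 2 reads "Adverse Event T T T T T/IE T T T IE IE". Set against the column heads, weeks 0 and 1 are blank, T (therapist) stands in every column from week 2 to weeks 16–20, week 10 has both T and IE (independent evaluator), and weeks 21 and 43 have IE alone.

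The Intervention section states the contrast: "We compare the UP with TAU intervention group with the waiting-list with TAU control group". On dose of contact, the UP section says that "patients will receive approximately 16 face-to-face, individual sessions (range: 9–20) within 20 weeks". For controls, the Follow-up phase section says: "Participants assigned to the control group will receive the unified protocol in addition to TAU during the follow-up period", that is, in weeks 21 to 43. The section on assessment procedure and blinding keeps the independent evaluators from allocation information.

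**The concern.** The number of solicited events recorded depends on how often patients are asked, by whom, and over what look-back. Here all three may differ by arm during the randomised period. UP patients are asked at their sessions by the person treating them, and again by a blinded evaluator. Waiting-list patients have only the evaluator.

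Several items on the list are also symptoms of the disorders under study, in patients who must score at least 8 on GRID-HAMD to enter. Such symptoms can come and go, so more frequent questions can record more events even if the true course is the same in both arms. If events from both sources go into one table by arm, part of any excess under UP would come from the collection rule. That table could also make mild or short-lived events on the waiting list look rarer than they are.

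**Working it through.** **1. Figures to reproduce.** The article gives no adverse event rate and no expected count, so there is no figure of its own to check. The inputs are the Table 2 schedule, the session range in the UP section, and the timing of UP for controls.

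**2. Whom the T cells can apply to.** Table 2 has no separate schedule by arm. The Homework Compliance Scale row has T in the same columns (week 2 to weeks 16–20), and the section on that scale says the raters are the therapists delivering UP. Controls receive UP only after week 21. The T cells before week 21 can therefore apply only to the UP arm. This is an inference from three places, not a statement in the article.

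**3. Enquiries up to week 21.** Table 2 has a therapist-rated session measure at week 1 but no adverse event entry there. Taking one enquiry per session and leaving out the week 1 session:

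UP enquiries = (sessions − 1) + 2 evaluator visits; control enquiries = 2.

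| Sessions | Therapist | Evaluator | UP total | Control total | Ratio |
|---|---|---|---|---|---|
| 9 | 8 | 2 | 10 | 2 | 5.0 |
| 16 | 15 | 2 | 17 | 2 | 8.5 |
| 20 | 19 | 2 | 21 | 2 | 10.5 |

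**4. Upper end of the effect on pooled counts.** Assume no true difference between arms, the same chance p of a report at each enquiry, independence between enquiries, and no recall of earlier events. Then

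P(at least one report) = 1 − (1 − p)^k, with k the number of enquiries.

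| p (assumed) | UP, k = 10 | UP, k = 17 | UP, k = 21 | Control, k = 2 |
|---|---|---|---|---|
| 0.01 | 10% | 16% | 19% | 2% |
| 0.02 | 18% | 29% | 35% | 4% |
| 0.05 | 40% | 58% | 66% | 10% |
| 0.10 | 65% | 83% | 89% | 19% |

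For p = 0.02 and k = 17: 1 − 0.98^17 = 0.291, against 1 − 0.98^2 = 0.040. With 27 patients per arm that is about 7.8 against 1.1 patients.

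**5. Lower end.** If each evaluator enquiry covers the whole time since the previous assessment and patients recall everything, the two control enquiries cover 10 + 11 = 21 weeks, and the share with at least one event is the same in both arms. The gap is then zero. It is also near zero if symptoms persist, because a symptom present all along is found at week 10 or 21 in either arm.

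**6. After restriction to evaluator entries.** Each arm has 2 enquiries by week 21, by blinded raters, so the ratio is 2/2 = 1.0.

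**The case against.** The case on the other side has several parts.

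- **No flawed analysis is stated.** The article specifies no between-arm comparison of adverse events. They are not among the primary or secondary outcomes, and the statistical methods cover efficacy measures. How they are tabulated commonly belongs in the analysis plan. This stands. A reader might infer that the trial's harms conclusion is biased, but the documents do not support that, since no pooled comparison is proposed. What remains is the collection rule, which the article itself fixes.
- **Comparable data already exist.** Table 2 schedules evaluator enquiries at weeks 10 and 21 without distinction by arm. A reader might conclude that adverse events cannot be compared between arms at all. That goes too far: the problem arises only if sources are pooled.
- **Worsening and suicidality are measured elsewhere.** Blinded evaluators rate GRID-HAMD, which has a suicide item, as well as CGI and SIGH-A at weeks 10 and 21. OASIS and ODSIS self-reports stand in every column. It is tempting to say that deterioration or suicidality in controls would go unseen. The documents do not support that. What could be missed is mainly transient episodes between visits.
- **The illustration is an extreme case.** Independence and no recall push the gap up, many listed symptoms tend to persist, and the evaluator form, which is not shown, may fix a look-back. This stands, and the range must reach down to zero.
- **Direction.** Pooled counts would run against UP, so they would not make UP look safer than it is. This also stands, though they could make the waiting list look more benign than it is.
- **Wording.** The limit to two enquiries holds only up to week 21. Controls are also asked at week 43, and may be asked by therapists once they start UP.

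**Conclusion.** The imbalance in enquiries is real and follows from the collection rule as written: up to week 21, about 17 enquiries in the UP arm (range 10 to 21) against 2 in control, with the extra 15 (range 8 to 19) made by an unblinded therapist. It rests on two readings: that the T cells before week 21 are UP sessions, and that the therapist asks at each session from week 2.

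The consequence is conditional. Any tabulation by arm that pools therapist and evaluator records would tend to inflate mild or transient solicited events under UP relative to control. The size cannot be fixed from the article. It runs from near zero, with full recall or persistent symptoms, to several-fold if events are brief and forgotten. Major events depend less on how often patients are asked. Evaluator-recorded events at weeks 10 and 21 do not share the imbalance.

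**What to change.** State that any between-arm comparison of adverse events over weeks 0–21 uses only events recorded by the independent evaluator at weeks 10 and 21, with the same checklist and the same look-back period in both arms. Define the look-back on the evaluator form if it is not already there. List therapist-recorded events in the UP arm separately, labelled by source, without a between-arm comparison.

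This needs analysis wording and, at most, one line on an existing form. It adds no visits and leaves the enquiries at therapy sessions as they are. Recruitment was still open when the article was submitted, with 44 enrolled. The restriction to evaluator entries uses data already scheduled, but a look-back added now would not cover assessments already done. The downside is that some transient events drop out of the comparison, though they stay in the listing.
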